**Figure 1 figure1:**
[figure not shown]
Patient flow diagram of the screening, brief intervention, and referral to treatment for adolescents: standard adolescent-only approach (SBIRT-A-Standard) versus SBIRT-A: family-based approach (SBIRT-A-Family) for adolescent substance use (SU) in the primary care multisite randomized effectiveness trial: recruitment, screening, randomization, and intervention recommendations. BNI: brief negotiated interview; FC: facilitated conversation; MH: mental health; RT: referral to treatment.

**Figure 2 figure2:**
[figure not shown]
The SPIRIT (Standard Protocol Items: Recommendations for Interventional Trials) checklist for the screening, brief intervention, and referral to treatment for adolescents: standard adolescent-only approach (SBIRT-A-Standard) versus SBIRT-A: family-based approach (SBIRT-A-Family) for adolescent substance use (SU) in the primary care (PC) multisite randomized effectiveness trial: schedule of trial enrollment, interventions, and assessments. AD: adolescent participant; AOD: alcohol and other drug; CG: caregiver participant; CL: clinician participant.

### Study Conditions

Both study conditions follow a similar set of procedures anchored in the use of handheld tablets. As depicted in Figure 1, tablets are used to collect screening data from youth and caregivers, calculate youth and family risk levels, and offer digitally supported BI and RT activities to users. Point-of-care digital SBIRT procedures can improve patient outcomes by facilitating more rapid and standardized services, data-informed clinical decision-making, and improved practice efficiency [16,51]. Both conditions feature 2 types of digital BIs: *patient facing* (ie, self-administered: patients navigate the BI alone on the tablet) and *provider facing* (ie, provider administered: providers and patients jointly navigate the BI on the tablet). The total time needed to deliver each approach matches the typical wait time for preventive visits plus time devoted to delivering comparable SBIRT-A procedures for youth identified as at risk in routine PC. Both conditions allow all youth and caregivers to speak with providers about AOD issues at any point they choose, in keeping with best practices honored at partner sites. When study interventions are not delivered during the main visit, providers can opt to complete interventions in a follow-up visit scheduled within 1 week or complete immediate handoff to an on-site behavioral health specialist (trained in all study procedures) to complete the intervention [21,52]. In addition, caregivers in both conditions are digitally prompted to enroll in a web-based suite of caregiver-focused resources (helpline, parent coaching, parent groups and electronic resources, and SMS text messaging) specifically designed to support youth AOD risk reduction and caregiver self-care [53].

### SBIRT-A-Standard Procedures

#### Screening (Approximately 2 Min)

All consented youth aged 12 to 17 years complete the CRAFFT (car, relax, alone, forget, friends, trouble) screening tool [54,55], which assesses the number of days during the past year and then the past 3 months during which various formulations of AOD were used, as well as whether they have ridden in a car whose driver was intoxicated; youth who respond negatively to all questions are categorized as *low risk*. If youth report >0 days of AOD use, the tool asks 5 additional questions assessing use risk and consequences; in addition, youth who report nicotine use in the past 30 days complete a nicotine dependence measure, the Hooked on Nicotine Checklist [56], modified to include nicotine vaping. Screening data are then used to sort youth into 3 risk categories: *riding risk only* (no reported AOD use but indicated rode in car driven by intoxicated person), *distant use* (reported AOD use in past year but not past 3 months), or *recent use* (reported AOD use in past 3 months). All screening data are summarized in a tablet-delivered clinician report to guide provider-facing intervention activities.

#### AOD Psychoeducation: All Risk Categories (Approximately 5 Min)

In the wait area, youth receive a tablet-delivered brief digital AOD education tutorial that includes advice to abstain from, or reduce, AOD use. The tutorial focuses on adolescent AOD prevalence rates and related behavioral symptoms, AOD use neurobiology and its relation to adolescent health, and common AOD impacts on developmental milestones [57]. Psychoeducation for AOD has shown positive effects as both a universal and selective prevention strategy [58,59].

#### Brief Negotiated Interview: Distant Use (Approximately 5 Min) and Recent Use (Approximately 8 Min)

In PC offices, youth and providers together complete a tablet-supported brief negotiated interview (BNI) [60]. The BNI is informed by AOD use data gathered during youth screening [61]. The BNI focuses on (1) education about AOD disorders, including youth and family factors that impact AOD use; (2) user-tailored feedback comparing the given youth’s AOD use and related problems to national norms, along with information on the neurobiological effects and developmental impacts of frequent use [32]; (3) motivational tools (eg, reduction readiness rulers) and decisional balance exercises (weighing positive vs negative personal impacts of AOD use) tailored to the youth’s use levels [62,63]; and (4) AOD reduction goal-setting interventions tailored to the youth’s readiness to change AOD use [64]. BNIs of this kind have demonstrated effectiveness in reducing AOD use and related problems [14,32,65].

#### RT: Recent Use (Approximately 5 Min)

In PC offices, providers and youth discuss the value of attending counseling services to address AOD-related problems [66] and counseling referral links that the PC site curates with local services, as well as the value of youth talking directly with caregivers about their AOD involvement as a first step toward support seeking and behavior change [45]. Providers directly recommend AOD counseling and facilitate a first appointment for youth who agree. The study team will continue to monitor and update curated referral lists with availability and wait-list times throughout the duration of the study.

### SBIRT-A-Family Procedures

#### Screening (Approximately 2 Min Apiece)

Screening procedures incorporate CRAFFT procedures for youth described for the SBIRT-A-Standard condition. They also incorporate two sources of caregiver-report data: (1) an assessment of caregiver beliefs about their child’s AOD use and worries about the impact of AOD use, and (2) a well-validated checklist of youth mental health problems [67] that yields clinical cut scores for 4 domains. If both youth and caregiver report no AOD use or clinically elevated mental health problem, the family is categorized as *low risk*. Otherwise, screening data are combined to sort families into 3 risk categories: *hidden substance use risk* (youth reports AOD use in past year; caregiver reports no youth AOD use in past year), *named mental health risk* (caregiver reports no youth AOD use in past year; caregiver reports clinical-level score for at least 1 youth mental health domain), and *named substance use risk* (caregiver reports youth AOD use in past year with or without reporting a clinically elevated mental health score). Adolescent and caregiver screening data are both summarized in the clinician report to guide provider-facing intervention activities.

#### AOD Psychoeducation: All Risk Categories (Approximately 5 Min Apiece)

Youth proceed as indicated in the SBIRT-A-Standard condition based on youth screening data. In the wait area, caregivers receive a tablet-delivered parenting tutorial that covers two AOD risk domains: (1) education about adolescent AOD use, including prevalence rates, related behavior problems, neurobiological and health effects, and impacts on developmental milestones; and (2) education and video modeling about parenting strategies that reduce or moderate AOD use risk, including positive communication, fair and consistent discipline, and nonjudgmental conversations about AOD use [68]. Positive parenting education has been shown effective as a universal and selective prevention strategy in parent-focused AOD prevention trials [69-71]. The tutorials are tailored for each risk category.

#### BNI: Named Substance Use Risk (Approximately 5 Min Apiece)

Youth proceed as indicated in the SBIRT-A-Standard condition based on youth screening data. In PC offices, caregivers and providers together complete a tablet-supported parenting BNI informed by data from the caregiver screening only that parallels the youth BNI (eg, AOD education and developmental risks) and also includes motivation, modeling, and goal setting on positive parenting (eg, nonjudgmental conversations) and effective parent-youth communication about AOD use (Multimedia Appendix 3) [41].

#### Facilitated Conversation: Named Substance Use Risk (Approximately 5 Min)

In PC offices, providers meet with youth and caregivers together to discuss the value of talking directly with the other family member about AOD risk. Providers convene a brief facilitated conversation coaching youth and then caregivers to speak directly to one another about AOD risk using positive communication skills presented to caregivers via wait area psychoeducation. In this conversation providers (1) emphasize that a positive youth-caregiver relationship is the strongest protective factor for youth development and (2) follow guidelines for brief triadic risk reduction interventions focused on positive family communication about AOD risk (Multimedia Appendix 4) [72]. This facilitated conversation is meant to follow the caregiver BNI. Providers may conduct the youth BNI (when indicated) before the caregiver BNI or after the facilitated conversation depending on preference and workflow.

#### RT: Named Substance Use Risk (Approximately 5 Min)

When indicated, providers directly recommend AOD counseling and facilitate a first appointment for families who agree (Multimedia Appendix 5).

### Intervention Training and Fidelity Monitoring

Site PC clinic staff who provide SBIRT-A to clinic patients are trained by experts in all intervention procedures for both conditions. We expect to train 10 providers per clinic. Providers attend a 1-hour site orientation followed by 3 hours of live training. First, providers complete a 1-hour introduction to motivational interviewing for adolescents, caregivers, and families. Next, providers attend two 1-hour live training sessions to apply motivational interviewing principles to support adolescent, caregiver, and family behavior change. The self-study training will include video-recorded presentations on motivational interviewing principles. Live training will include a review of counseling steps for each intervention, video-recorded counseling demonstrations, and opportunities to practice counseling steps. These training procedures have been successfully implemented in similar PC SBIRT studies [16,31]. Baseline fidelity is established via a 1-hour individual counseling practice with research staff. Thereafter, providers attend a monthly 1-hour clinical consultation meeting held by authors MB and [name] to maintain and enhance intervention skills, review notable clinical encounters, and troubleshoot procedural and technology challenges. In addition, providers will complete practice interventions using standardized case vignettes on a 6-month cadence. Vignette scenarios will be informed by implementation experiences shared by providers during the course of the consultation period; these serve as training refreshers and will also provide fidelity feedback data to be incorporated in consultation meetings, as will data summarized from the provider self-report fidelity checklist described in the next subsection [73].

### Fidelity Measures

A provider self-report fidelity checklist is collected after every encounter with every family. The checklist assesses information on which the provider-facing intervention components were delivered: adolescent BNI, caregiver BNI, facilitated conversation, or RT. Checklist items feature 3-point Likert-type rating scales to indicate how clinically helpful the given component was for the encounter: *not at all*, *somewhat*, or *very*. The checklist also logs (1) which implementation scenario was selected for intervention delivery: pediatrician intervention during visit, pediatrician follow-up visit, or behavioral specialist intervention on the visit day; (2) whether the intervention occurred in person or via video call; and (3) the number of minutes spent delivering the intervention or interventions. Research indicates that clinicians can reliably self-report on the delivery of behavioral interventions with families using brief postencounter fidelity checklists [74-76]. In addition, during initial follow-up assessment, adolescents and caregivers report on which components they experienced during the encounter: psychoeducation, BNI, facilitated conversation, or RT.

### Outcome Measures: Screening Interview

CRAFFT [54,55] is a widely used and well-validated youth report tool that measures patient use of alcohol, cannabis, nicotine, illegal drugs, prescription medication, or anything else to get high in the past year and the past 3 months. It also asks about riding in a car driven by someone (including self) who was intoxicated (described in the SBIRT-A-Standard Procedures subsection). If AOD use is reported, the tool asks 5 additional questions: “Do you ever use alcohol or drugs to relax, feel better about yourself, or fit in?” “Do you ever use alcohol or drugs while you are by yourself [alone]?” “Do you ever forget things you did while using alcohol or drugs?” “Do your family or friends ever tell you that you should cut down on your drinking or drug use?” “Have you ever got into trouble while you were using alcohol or drugs?” The Hooked on Nicotine Checklist [56] is a 10-item youth report of nicotine dependence completed by patients who report any days of using a vaping device containing nicotine, or any tobacco products, during the past 30 days. Parent-Adolescent AOD Communication Frequency [77] is a 6-item youth and caregiver report of how often parents and teens talk to one another about key AOD issues (eg, the health risks of use and discipline regarding use) scored on a 5-point scale ranging from *never* to *very often* [78-80]. Parent-Adolescent AOD Communication Quality [81] is a 6-item youth and caregiver report of the quality of communication between parent and teen about AOD issues (eg, “My caregiver/teen and I are interested in each other’s opinions about AOD” and “If my caregiver/teen and I talk about drugs, I feel understood”) scored on a 5-point scale ranging from *not at all* to *very much* [41,77]. Beliefs and Worries about Youth AOD Use is an 8-item measure that asks caregivers what they believe about their teen’s use of AOD in the past year and in the past 3 months (response options: “I am sure or pretty sure my teen has not used,” “I suspect but I am not sure my teen has used,” and “I am sure or pretty sure my teen has used”). Follow-up questions ask which substances they believe their teen has or may have used and their worries about the impact of their teen’s use of AOD across contexts (ie, home, school, peers, and safety). This measure was created for this study, inspired by the Screening to Brief Intervention tool [8] and the CRAFFT tool [55] and vetted by SBIRT experts. The Brief Problem Monitor is a 19-item caregiver report component of the well-validated Achenbach youth behavior problem assessment system [67] that yields normed scores with clinical cut levels for 4 problem domains: internalizing (anxiety, depression, and somatic complaints), externalizing (aggression and conduct problems), inattention or impulsivity, and total problems [82].

### Outcome Measures: Follow-Up Interviews

The timeline followback (TLFB) method [83] is the gold standard method for collecting youth report retrospective estimates of AOD use using a calendar visual aid to facilitate recall. This study used a computer-administered and calendar-assisted instrument created for REDCap-compatible remote asynchronous follow-up assessment modeled after the TLFB [31]. This version assesses the number of days that youth used alcohol, tobacco, marijuana, non–medical prescription drugs, inhalants or vapes, and herbs or synthetic drugs over the past 90 days. If alcohol was used, follow-up questions assess binge drinking episodes. The KIDSCREEN-27 questionnaire (youth and caregiver report) [84] measures youth functioning in social and school domains. Items assess the degree to which youth have experienced problems with a specific task or activity during the past month. It is internationally used and has excellent psychometric properties with strong construct validity and test-retest reliability [84,85]. The Services Assessment for Children and Adolescents (caregiver report) [86] assesses the youth’s past and current use of inpatient, outpatient, and school-based behavioral health services. It has shown strong validity and test-retest reliability [87] as well as interrater reliability between parent and child reports [88]. Items were added to assess caregiver enrollment and the use of web-based educational and support resources for adolescent AOD. Perceived Risk (youth report) [89] asks youth to rate the degree to which people risk harming themselves if they use various categories of substances on a 4-point scale ranging from *no risk* to *great risk*. Peer Deviance (youth report) [89] assesses the number of peers who use various substances on a 5-point scale ranging from *none* to *all*. Parent Rules about Substance Use (youth and caregiver report) [90] assesses parent rules about using various substances on a 6-point scale ranging from *not allowed to use AOD* to *no rules about using AOD*. The Family Assessment Device (youth and caregiver report) [91] assesses family relationships, communication, and problem-solving on a 4-point scale ranging from *strongly agree* to *strongly disagree*. The Comprehensive Adolescent Severity Inventory (youth report) [92] assesses academic achievement, school connection, and disciplinary record. Youth-Provider Connectedness (youth report) [93] assesses the level of trust and connection adolescents feel toward their health care providers on a 5-point scale ranging from *not at all* to *very much*. Psychoeducation Knowledge (caregiver report; created for this study) assesses caregiver knowledge of the tablet-delivered AOD psychoeducation. The Parent-Adolescent AOD Communication Frequency measure, Parent-Adolescent AOD Communication Quality measure, and Brief Problem Monitor (all described in the previous subsection) are also administered at follow-up to youth and caregivers.

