#### Aim 2 and Aim 3 Analyses

Aim 2 evaluates the comparative effectiveness of study conditions on AOD risk factors (eg, peer conduct problems, susceptibility to peer pressure, school problems, and family functioning), co-occurring problems (internalizing, externalizing, and impulsivity), quality of life, and parent-adolescent AOD communication. A similar modeling approach to aim 1 is used, the primary difference being that all outcome variables are continuous rather than ordinal; as such, standard mixed effects growth models [97] are used to compare intervention effectiveness. Aim 3 compares the rates of behavioral counseling service use between the conditions. Differences are tested at 1-year follow-up using a simple logistic regression model with a binary *yes/no* outcome variable indicating whether the youth received any counseling during the study period. Higher rates of counseling use are expected in the SBIRT-A-Family condition.

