Importantly, this trial also emphasizes patient-centered outcomes research methods in several ways. It is recruiting participants representative of the full spectrum of adolescents and caregivers attending PC visits. Both SBIRT-A approaches rigorously protect the privacy and confidentiality of both youth and caregivers; neither learn directly or indirectly about the confidential information collected from the other person on surveys or during provider interviews without expressed permission to share such data. All SBIRT-A procedures can be delivered by trained staff across the PC provider spectrum: nurse practitioners, physicians, physician assistants, behavioral counselors, and so forth [108]. These patient-centered design features enhance the consistency and effectiveness of SBIRT-A delivery in PC.

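### Aim 3 counseling use is reported by caregivers alone, and the two referral procedures can leave caregivers unequally informed, so counseling could be under-counted more in SBIRT-A-Standard; the size of any bias is unknown

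*Protocol article*

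**What the plan says.** **Instrument.** Under Outcome Measures: Follow-Up Interviews, service use is covered by one measure: "The Services Assessment for Children and Adolescents (caregiver report) [86] assesses" past and current behavioral health services. The same section marks several other measures (KIDSCREEN-27, Parent Rules about Substance Use, the Family Assessment Device) as completed by both youth and caregiver, so the single reporter looks like a deliberate choice. In support, the section cites validity, test-retest reliability and "interrater reliability between parent and child reports", without a figure. The article describes no youth report, record check or appointment log of counseling attendance.

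**Outcome and test.** Aim 2 and Aim 3 Analyses compares the arms at 1 year with a "simple logistic regression model with a binary" outcome "indicating whether the youth received any counseling during the study period". The section does not name the instrument, but only one of those described covers the outcome. The expected direction is stated: "Higher rates of counseling use are expected in the SBIRT-A-Family condition". The Abstract lists therapy attendance as a secondary outcome.

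**Referral by arm.** In Standard, for recent use: "Providers directly recommend AOD counseling and facilitate a first appointment for youth who agree". That section also has the provider discuss the value of the youth talking to the caregiver. In Family, for named substance use risk, providers "facilitate a first appointment for families who agree".

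**Confidentiality.** For both arms, the Discussion summary says that "neither learn directly or indirectly about the confidential information collected from the other person on surveys or during provider interviews without expressed permission".

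**The concern.** A comparison of counseling rates is fair only if counseling that took place has the same chance of being recorded in each arm. Here the person who records it is also someone whose involvement the randomized condition changes. A Family caregiver in the named substance use category takes part in arranging the appointment. A Standard caregiver may hear of it only if the youth chooses to say so.

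If some Standard youth attend counseling their caregivers do not know about, those cases are recorded as no counseling. The observed Family-minus-Standard difference then includes a gap in caregiver knowledge as well as any real difference in attendance. Because that gap would most plausibly run in the hypothesized direction, a positive Aim 3 result could not be fully separated from better-informed caregivers. Nothing the article describes collecting would show how much of the difference is due to each.

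**Working it through.** **Plan's own figure.** Study Power expects power above 0.95 for Aim 3 but gives no counseling rate or difference, so the figure cannot be reproduced. As a check on sample size and alpha only, the Aim 1 12-month proportions (67.9% versus 78.4%) with 800 per arm give two-proportion power of 0.997, against the stated simulation result of 0.99. This is an end-point approximation, not the slope simulation.

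**Inputs from the article.** 1,600 at-risk youth at 1 year; recent use about 36% of the full sample (both Study Power).

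**Inputs assumed.**
- 800 per arm (1:1) and a two-sided .05 test, before any false discovery rate adjustment.
- True counseling use p equal in both arms.
- Caregivers unaware of a share u of counseled youth in Standard and v in Family.
- Caregivers do not report counseling that did not occur.

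**Formulas.**
- Observed Standard rate s = p(1 − u); observed Family rate f = p(1 − v).
- h = 2·arcsin√f − 2·arcsin√s, and z = h·√(800/2) = 20h.
- Rejection probability = Φ(z − 1.96) + Φ(−z − 1.96). It should be 0.05, since there is no true difference.

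**Results at p = 20%.**

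1. *Equal unawareness* (for example u = v = 20%): 16% versus 16%, odds ratio 1.0, rejection 0.05. There is no bias.
2. *25% versus 5%, excess confined to recent-use youth, assumed to be 36% of those counseled:* u = 0.36 × 0.25 + 0.64 × 0.05 = 0.122. Then s = 0.20 × 0.878 = 17.6% and f = 0.20 × 0.95 = 19.0%. Odds ratio 1.10, h = 0.037, z = 0.75, rejection 0.12. A pooled-variance formula counting only results favoring Family gives 0.11.
3. *As 2, but recent-use youth are 70% of those counseled:* u = 0.70 × 0.25 + 0.30 × 0.05 = 0.19. Then s = 16.2% versus f = 19.0%, rejection 0.31.
4. *25% versus 5% among all counseled youth:* s = 15.0% versus f = 19.0%. Odds ratio 1.33, h = 0.107, z = 2.13, rejection 0.57.

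**Other true rates.**

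| True use | Scenario 2 | Scenario 4 | 15% vs 5%, all counseled | 10% vs 5%, all counseled |
|---|---|---|---|---|
| 10% | 0.08 | 0.30 | 0.11 | 0.06 |
| 20% | 0.12 | 0.57 | 0.18 | 0.08 |
| 30% | 0.16 | 0.79 | 0.27 | 0.10 |

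**Sensitivity within the 36% share.** If caregivers miss 40% of the counseling in that group and nothing else in either arm, u = 0.36 × 0.40 = 0.144. The observed rates are 17.1% versus 20.0% and rejection is 0.32. Confining the mechanism to recent-use youth reduces the effect but does not by itself make it negligible.

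**The case against.** A reader might infer that counseling is in fact under-counted in Standard and that Aim 3 is therefore biased toward Family. The documents do not support that, for these reasons:

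- **No rates.** The article gives neither a counseling rate nor a share of caregivers who are unaware.
- **Caregivers are usually needed.** The introduction (Strengthen RT Linkages) says that enrolling teenagers in such services typically takes caregiver involvement. The outcome is counseling received, not referral offered. A referral kept from the caregiver may often lead to no counseling, and that would be a true difference, which Aim 3 is meant to detect.
- **Confidentiality is narrower than it may seem.** The Discussion statement protects information given in surveys and provider interviews, in both arms. It does not say that later attendance is hidden from caregivers. That the Standard referral is made in confidence is inferred from two sections read together.
- **The arm contrast is partial.** Standard referral reaches recent-use youth only. Family referral with the caregiver is described for named substance use risk. Youth in the hidden-risk category, whose caregivers report no use, may also have care their caregivers do not know about.
- **Much counseling arises elsewhere.** The outcome is any counseling, including school-based and other services unrelated to the study referral.

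These points stand, and they make the lower part of the range more plausible. They do not remove the risk. Typical caregiver involvement is not universal involvement, encouragement to disclose is not disclosure, and general parent-child agreement does not show that agreement is equal between arms. School-based care is also a service a caregiver may not know about.

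**Conclusion.** The concern holds as a risk of differential outcome ascertainment. Aim 3 depends on one reporter, whose knowledge the assigned condition can change, and any resulting under-count would most plausibly favor Family. Whether it occurs, and how large it is, cannot be established from the article.

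Under the assumptions above (20% true use in both arms, 800 per arm, two-sided .05), the false-positive rate runs from 0.05 with equal unawareness, through 0.11 to 0.12 when a 25% versus 5% gap is confined to a 36% recent-use share, to 0.57 when it covers all counseled Standard youth. The last figure is an upper illustration, not an expected value.

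Severity is moderate. The outcome is secondary, and the Aim 1 substance use outcome is youth-reported and not affected. The point is worth acting on because the trial as described could not detect the bias if it were present.

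**What to change.** 1. Give youth in both arms the same service-use items at all remaining follow-ups. Ask those already past earlier waves to recall back to the primary care visit. Youth know whether they attended counseling regardless of arm, and the article itself cites agreement between parent and child reports for this instrument.
2. By amendment, before any comparison by arm, define Aim 3 counseling as reported by either youth or caregiver, and state how a case with only one respondent is handled.
3. Report the caregiver-only result as a sensitivity analysis, with youth-caregiver agreement shown separately by arm. Similar agreement in the two arms would be reassuring; lower agreement in Standard would show the problem and its approximate size.

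**Cost.** A few items are added to a youth assessment that already takes about 20 minutes. There is some recall error for past waves. A secondary outcome changes after recruitment began in March 2024, which must be documented and, under Ethical Considerations, approved by the institutional review board and the data safety and monitoring board. Waiting adds to the recall burden.
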